## Abstract

**Background:**

Approximately 40–70% of people with Parkinson’s disease (PD) fall each year, causing decreased activity levels and quality of life. Current fall-prevention strategies include the use of pharmacological and non-pharmacological therapies. To increase the accessibility of this vulnerable population, we developed a multidisciplinary telemedicine program using an Information and Communication Technology (ICT) platform. We hypothesized that the risk for falling in PD would decrease among participants receiving a multidisciplinary telemedicine intervention program added to standard office-based neurological care.

**Objective:**

To determine the feasibility and cost-effectiveness of a multidisciplinary telemedicine intervention to decrease the incidence of falls in patients with PD.

**Methods:**

Ongoing, longitudinal, randomized, single-blinded, case-control, clinical trial. We will include 76 non-demented patients with idiopathic PD with a high risk of falling and limited access to multidisciplinary care. The intervention group (n = 38) will receive multidisciplinary remote care in addition to standard medical care, and the control group (n = 38) standard medical care only. Nutrition, sarcopenia and frailty status, motor, non-motor symptoms, health-related quality of life, caregiver burden, falls, balance and gait disturbances, direct and non-medical costs will be assessed using validated rating scales.

**Results:**

This study will provide a cost-effectiveness assessment of multidisciplinary telemedicine intervention for fall reduction in PD, in addition to standard neurological medical care.

**Conclusion:**

In this challenging initiative, we will determine whether a multidisciplinary telemedicine intervention program can reduce falls, as an alternative intervention option for PD patients with restricted access to multidisciplinary care.

**Trial registration:**

**ClinicalTrials.gov Identifier**: NCT04694443.

## Background

The Parkinson’s disease (PD) population is mainly sedentary, causing a dramatic reduction of physical activity compared to healthy older adults, even early in the disease [1, 2]. As PD progresses, falls are often harmful and very common [3]. Approximately 40–70% of people with PD fall each year, and one-third fall repeatedly [3, 4]. twice as likely as the healthy elderly population [5]. Evidence shows that falls significantly impact people’s lives with PD, including debilitating effects on confidence, decreased activity levels, and reduced quality of life [6–8]. Consequently, repeat falls are a risk factor that implies subsequent falls, often with such consequences as fractures, prolonged immobility and dependency, social isolation, and financially costly individuals and healthcare systems [9].

Although falling increases with disease severity, falls are even common in the early stages of the condition [10]. Anti-parkinsonian drugs are the main treatment to counter the symptoms that can cause PD patients to fall, while research into finding a cure continues. However, medication cannot adequately control reduced postural control and prevent falls, especially among patients with advanced PD [4]. Other fall-prevention strategies include educational support, physical exercise, and modification of environmental factors [3, 5, 8]. In this regard, behavioral change strategies provide a theoretically based approach for helping patients with PD develop the skills they need (e.g., goal setting, self-monitoring) for successful engagement in sustained exercising, and therefore fall prevention [11]. Randomized clinical trials published in the literature have concluded that exercise as a single intervention can prevent falls among community-dwelling patients with PD and can be particularly beneficial for maintaining postural control, mobility, and daily living activities [12]. Also, there is growing evidence that remote monitoring of physical activity is also feasible in neurological diseases, including PD [11, 13]. In Spain, PD associations often offer long-term physical non-pharmacological therapies for PD, including physical, occupational, speech therapies, and psychological support. Based on the estimated average prevalence rates of PD in Spain of 682.2/10^5^ (IC: 127.4/10^5^−1491.7/10^5^) [14], but only 14% of these patients receive non-pharmacological therapies provided by PD associations (Spanish PD Association. Unpublished data). This scenario has even worsened during the Covid-19 pandemic.

In this regard, the role of Information and Communication Technologies (ICT) in a home fall prevention program for patients living with PD could be crucial and a promising, cost-effective strategy, with the added advantage of reaching PD patients remotely [15, 16]. Different software solutions have been described on telerehabilitation, such as the Platform of Telemedicine (Teleriab), designed to offer telerehabilitation services. Health staff can contact patients through this web platform either over the phone or by using a videoconferencing option with one or more patients simultaneously or consecutively, respecting the patients’ privacy [17]. Other authors have provided telerehabilitation through videoconferencing via a smartphone or iPad with a (digitally simulated) avatar coach [18–20]. Previously, most published reviews have discussed only the short-term benefits of rehabilitation for people with PD. Studies designed to analyze the feasibility and cost-effectiveness of multidisciplinary telemedicine programs for fall prevention in PD are needed. Given the lack of scientific evidence, we hypothesized that a multidisciplinary telemedicine intervention program added to a standard in-office neurological care would be more effective than standard in-office neurological care to decrease the incidence of falls in PD. This study describes the methodology of a clinical trial designed to analyze the feasibility and cost-effectiveness of a low-cost telemedicine multidisciplinary telemedicine program to reduce the incidence of falls in addition to in-office usual care in a population with PD.

## Materials and methods

### Design

This study is a clinical trial protocol related to a future randomized controlled trial of an 8-month-follow-up study, multidisciplinary home-based telerehabilitation intervention, single-center, case-control, single-blinded, longitudinal, 8-month-follow-up study. This study is registered on clinicalTrials.gov Identifier, with the registration number NCT04694443. The protocol of this study followed the SPIRIT reporting criteria for protocol reports [21]. We will conduct this study at the Movement disorder unit of a tertiary hospital, Hospital Universitario Burgos, in collaboration with the Health Science and the Computer Engineering School at the University of Burgos, Spain.

### Specific goals

The first objectives of this study are to study and compare the intervention vs. the control group, in terms of 1) the reduction of fall incidence (total number of falls from baseline) with the implementation of an additional multidisciplinary telemedicine program; and 2) the cost-effectiveness of this telemedicine program compared to usual care. Secondary objectives are: 1) to study the feasibility and patients’ adherence to new technology (defined as patients retention > 80% during the study), 2) to study the clinical utility of using wearable sensors to monitor gait dysfunction and physical activity, 3) to analyze the duration of clinical benefits after finishing a telemedicine program (short-term vs. long-term benefits), and 5) to develop a full-stack using Big Data frameworks that facilitate communication between the patient and the occupational therapist using Artificial Intelligence (AI) techniques.

### Study population

We will invite non-demented, ambulatory patients aged > 18 years old, with established idiopathic PD based on the MDS-criteria [22, 23], with a medium-high risk of falling established by a history of at least one fall in the previous 12 months with a Hoehn & Yahr (HY) stage < 3 [24], a Montreal Cognitive Assessment (MoCA) score > 18 [25], without access to non-pharmacological therapies, and one of the two additional criteria including the presence of freezing of gait (FOG) or self-selected gait speed < 1.1 meters/second [26]. We will exclude patients with severe psychiatric or cerebrovascular diseases, severe traumatic head injuries, severe orthopedic lower limb or spine problems, peripheral neuropathy, rheumatological disease, or other systemic diseases or sensory deficiencies that, according to the investigator’s judgment, may interfere with the study.

### Ethical considerations

This study will be conducted according to the standards for Good Clinical Practice, the fundamental ethical principles established in the Declaration of Helsinki and the Oviedo Convention, and the requirements established in Spanish legislation in the research field. This project has been approved by the Comité Ético Complejo Universitario Burgos y Soria (Certificate number: CEIC 2112, October, 29^th^, 2019). All patients will read and sign the informed consent form before participating. The researchers will ensure that the anonymity of the participants is protected, and the data concerning people will remain confidential so that their identities and any identifying information are protected. The clinical records, research instruments, or any used documents that contain data from the participants will not be identified by the participant’s name but rather by a code, even when the information is submitted to regulatory institutions or sponsors. The researchers will protect the participants’ records, and the information on the codes, names, and addresses of the participants will remain confidential and available only to the researchers. Two copies of the consent forms will be provided, both of which will be signed by the participants, researchers, and guardians (or legal representatives). The researchers will store all files in a secure location in a single folder dedicated to this study. If a participant does not follow these rules, he or she will receive an original copy of the consent form. The results of this research may be presented at meetings or publications; however, the participants’ identities will not be revealed in these presentations.

The risks during the research are minimal or nonexistent, but the assessments and rehabilitation procedures may cause discomfort due to balance problems. If discomfort is experienced, the evaluations may be paused until medical interventions are performed, if necessary. However, if discomfort persists, the participant will be removed from the research, the data collected will be excluded from analysis, and the patient will not be reallocated to another group

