## Procedure

After signing the informed consent form, investigators will invite PD patients to participate in this randomized controlled trial. Patients will be randomly assigned using a block gender-randomization Excel calculator [male/female: intervention/control groups), providing an equal number of males and females with PD in the control/intervention groups (1:1). There will be no personal expenses for the participant during the study; instead, all assessments will be free, including the neurologist, nurse, psychologist, and occupational therapist evaluations. The patients will be contacted by phone to confirm they attended the treatment sessions. Likewise, reports of the assessments performed during the study will be available to improve patient adherence to the intervention protocols.

Two study phases will be established (Fig 1). In the *first phase* (baseline-4^th^ month), short-term benefits will be assessed. All participants will be evaluated at baseline and four months in office. Patients allocated in the intervention group will be receiving the telemedicine fall prevention program. The occupational therapist will bring the equipment for videoconferencing to the patients’ home, set up the room for physical therapy, and evaluate the patient’s risk of performing different exercises according to the patient’s capabilities and home environment. In the *second phase* (5^th^-8^th^month), long-term benefits will be assessed. All patients allocated in the intervention group will discontinue the telemedicine program at the end of the 4^th^ month. All patients will receive standard medical care provided by the movement disorder neurologist and nurse, with a final visit at eight months from baseline.

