### Virtual visits

Telemedicine visits in the intervention group will include telerehabilitation, neurologist and nurse telecare, and tele-support groups conducted by the psychologist (Fig 3). Tele-rehabilitation will consist of an individualized program with each of the patients, 45 to 60 minutes long. All sessions will be directed and supervised in real-time by the occupational therapist. During these telerehabilitation sessions, the occupational therapist will give the patient the necessary instructions to perform various exercises. First, a prior physical warm-up, consisting of a series of mobility exercises and stretching, followed by exercises designed to improve body posture, increase mobility, favor transfers, reduce axial stiffness, freezing, and walking disturbances, and enhancing balance and coordination, according to the cognitive, sensory-motor training therapy (Perfetti method) [28, 29]. During this cognitive sensory-motor training therapy, motor control will be improved using a specific type of repetitive sensory and motor re-learning protocol. Different exercises will be accommodated based on the patient’s capacity, including kinesthetic tasks [simple to complex parameter movement discrimination] with the corresponding cognitive activity [recognition of the direction and distance of the movement], and coordination tasks associated with executive cognitive activity [28, 29].

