## Statistical analysis

### Sample size

We calculated the sample size using the Epidat^®^ 4.1 statistical software. Considering that a 50% fall reduction in the number of falls compared to baseline will be obtained in 24% of the participants in the intervention group and 2% in the control group, we estimated that 70 patients (35 per group) would provide 80% power (5% probability of type 1 error) with a confidence level of 95%. By assuming a 9% dropout rate, a total sample of 76 patients will be then included in this study.

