### Outcome measures

The study’s primary outcome measure will be the total number of falls in the 4-month (short-term benefit) and 8-month (long-term benefit) after randomization. A fall will be defined as unintentionally coming to rest on the ground or other lower surface without overwhelming external force or a major internal event [56].

Other secondary outcome measures will include: 1) Cost-effectiveness, which will be estimated using natural units of health outcomes, including the incremental cost-effectiveness ratio per fall prevented and cost per extra person avoiding mobility deterioration (identified as an average number of daily steps assessed by wearable sensors); 2) A cost-utility analysis using the EuroQoL will estimate the incremental cost per quality-adjusted life-years (QALY) gain; 3) Short and long-term rate of change from baseline to four and eight months, respectively of motor, NMS, gait, balance, HR-QoL, caregiver burden, and comorbidities severity; 4) Feasibility (completed telemedicine visits) and adherence (dropout rate of telemedicine visits).

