### Statistical analysis

The study includes several necessary methodological resources that will minimize the risk of bias, such as the randomization process, allocation concealment, blinded assessment of the results, and intention-to-treat analysis. A statistician blinded to group allocation will supervise the data entry and analysis. The normality of the variables will be evaluated using the Kolmogorov-Smirnov test and graphs, including histograms and normal distribution plots. For the description of the quantitative variables, the mean and the standard deviation will be used, and for categorical variables, the frequency distribution and percentages. For non-normally-distributed variables, we will use the median, the interquartile range, and the corresponding non-parametric tests. The association between independent categorical variables will be analyzed using the χ2 test or Fisher’s exact test. The means between the two groups will be compared using the one-way analysis of variance (ANOVA). We will analyze the relationship between quantitative variables using correlation coefficients.

We will use logistic regression models to analyze the relationship between fall strategy prevention of 50% reduction in the incidence of falls (yes vs. no) as the dependent variable with the intervention vs. the control group, as the independent variable adjusted for age, gender, total motor MDS-UPDRS, comorbidity severity, and total levodopa equivalent dose. Other pertinent univariate and multivariable analyses will be performed based on the objective type. Also, given the complexity of potential analysis, including a diversity of variables from different origin and measurement properties, advanced statistical methodology (data mining, AI techniques) will be applied as needed. The level of significance will be set at p < 0.05. Statistical analysis will be performed with SPSS V.25.0. (IBM SPSS Statistics for Windows, Armonk, NY, USA).

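### Excluding the data of participants removed for persistent discomfort contradicts the stated intention-to-treat analysis and could bias the fall comparison

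*Protocol article*

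**What the plan says.** The Ethical considerations section warns that "the assessments and rehabilitation procedures may cause discomfort due to balance problems". Evaluations may then be paused. If the discomfort persists, "the participant will be removed from the research, the data collected will be excluded from analysis", and the patient is not moved to another group. That last clause shows that the rule concerns participants already allocated, not screening failures.

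The Statistical analysis section lists among its safeguards against bias "blinded assessment of the results, and intention-to-treat analysis".

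On exposure to the trigger, the Procedure section says "All participants will be evaluated at baseline and four months in office", and a final visit for all follows at eight months. Of the first four months it also says "Patients allocated in the intervention group will be receiving the telemedicine fall prevention program". The Virtual visits section adds "Telemedicine visits in the intervention group will include telerehabilitation, neurologist and nurse telecare".

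On the outcome, the Outcome measures section says "The study’s primary outcome measure will be the total number of falls in the 4-month (short-term benefit) and 8-month (long-term benefit) after randomization".

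**The concern.** Intention-to-treat means that randomised participants are analysed in the group to which they were assigned. A rule that discards data already collected, because of an event after randomisation, does the opposite. Nothing in the article confines the exclusion to a per-protocol or other secondary analysis set. An analyst who follows one section must therefore breach the other.

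The reason for exclusion is not neutral. Balance problems are closely tied to falling, so excluded participants may well have higher fall rates than those who remain. The chance of meeting the trigger also differs by arm. Both arms have the in-office assessments, but only the intervention arm also has supervised exercise sessions. If more participants with poor balance are dropped from that arm, those left could show fewer falls per person even if the programme does nothing. The cost per fall prevented would carry the same bias. The blinded statistician named in the Statistical analysis section cannot restore data excluded before analysis.

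**Working it through.** **1. The passages side by side.**
- Who: allocated participants with persistent discomfort (Ethical considerations).
- When: after randomisation, during assessments or rehabilitation.
- Consequence: data already collected leave the analysis.
- Stated principle: intention-to-treat (Statistical analysis).
- Reconciling text: none in the article.

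The contradiction needs no arithmetic.

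**2. The plan's own figures.** The sample size assumes that a 50% reduction in falls "will be obtained in 24% of the participants in the intervention group and 2% in the control group". A two-sided 5% test of two proportions with pooled variance and 80% power needs 36 per arm, against 35 stated. Power at 35 per arm is 79.4%. Inflating for dropout gives 70 / (1 − 0.09) = 76.9, so 77 against 76 stated. The figures agree within rounding and choice of formula, and the point does not rest on them. Power at the full 38 per arm is 82.7%, so keeping everyone costs none.

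**3. Size of a possible bias on total falls.** The article gives no removal frequency, so everything here is assumed: no true effect, individual fall rates exponentially distributed with mean 1, and a fraction q excluded from the intervention arm only.

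*Exclusion in proportion to fall rate.* The excluded have mean rate 2, so the remainder has mean (1 − 2q)/(1 − q).
- q = 1/38: 36/37 = 0.97
- q = 2/38: 34/36 = 0.94
- q = 10%: 0.80/0.90 = 0.89

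*Exclusion of exactly the highest-rate fraction.* The remainder has mean [1 − q(1 + ln(1/q))]/(1 − q).
- q = 5%: 0.84
- q = 10%: (1 − 0.1 × 3.303)/0.9 = 0.74
- q = 15%: 0.67

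*Exclusion in both arms, in proportion to fall rate.*
- 6.7% intervention, 3.3% control: (0.866/0.933) / (0.934/0.967) = 0.928/0.966 = 0.96
- Same fraction and same mechanism in both arms: 1.00

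**4. The 50% reduction endpoint.** This is the outcome in the sample size and the logistic regression. It compares each participant with his or her own baseline, so a high fall rate does not by itself make someone a non-responder. If every excluded participant were a non-responder, a true 24% would become 0.24 × 38/36 = 25.3% with 2 excluded and 0.24 × 38/32 = 28.5% with 6 excluded. Without that assumption, neither direction nor size is established here.

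**The case against.** A reader might infer that the rule strips the least stable participants mainly from the intervention arm and so manufactures a fall reduction. The documents do not support that much. In-office assessments, including balance and mobility tests, are done in all participants and can trigger the rule in either arm. Telerehabilitation is adapted to each patient's capacity and home. The trigger is discomfort, not a measured fall rate. Unequal exposure is a fair inference, but a majority of removals in one arm is not shown.

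The larger figures are also easy to overread. A 10% or 15% exclusion in one arm for discomfort alone exceeds the 9% dropout planned overall, and the article describes the research risks as minimal or absent. Zero exclusion in the control arm is the extreme case. With one or two exclusions, or similar exclusions in both arms, the bias is slight or nil. Nor are such participants necessarily hidden, since retention and dropout from telemedicine visits are assessed in their own right, although the article does not say how removals count there.

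All of this stands as a limit on size and direction. None of it reconciles the two sections. A separate analysis plan could not do so either: it would have to depart from one of two explicit statements.

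**Conclusion.** The point holds as a contradiction in the text: the exclusion rule and the intention-to-treat statement cannot both be followed. The exclusion arises after randomisation, is plausibly related to falls and may be more frequent in the intervention arm, so it could favour the intervention.

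How much is unknown. The illustrations for total falls run from no bias to an apparent reduction of about a quarter at 10% excluded. The upper end requires exclusion in the intervention arm only and of exactly the most frequent fallers. The need for correction rests on the contradiction and on how easily it is removed, not on any one of these figures.

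**What to change.** In the Ethical considerations section, delete the clause that excludes collected data from the analysis, so that it agrees with the Statistical analysis section. In its place state that:
- all randomised participants are analysed in their allocated group, using all data collected up to removal and any later data that the investigators can obtain with consent;
- the number of removals and the reasons are reported by arm.

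When a participant pauses or stops procedures, or leaves the study, is for the investigators and is not questioned here. No continued visits are asked for.

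The cost is about one sentence of protocol text and a line in the participant flow report. The sample stays at 76 and no new visits are needed. Whether the ethics committee must be notified is not stated in the article; if so, that is an added administrative step.
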